# Study protocol of EMPOWER Participatory Action Research (EMPOWER-PAR): a pragmatic cluster randomised controlled trial of multifaceted chronic disease management strategies to improve diabetes and hypertension outcomes in primary care

**DOI:** 10.1186/1471-2296-15-151

**Published:** 2014-09-13

**Keywords:** Chronic disease management, Chronic care model, Multifaceted intervention, Primary care, Type 2 diabetes mellitus, Hypertension

## Abstract

**Background:**

Chronic disease management presents enormous challenges to the primary care workforce because of the rising epidemic of cardiovascular risk factors. The chronic care model was proven effective in improving chronic disease outcomes in developed countries, but there is little evidence of its effectiveness in developing countries. The aim of this study was to evaluate the effectiveness of the EMPOWER-PAR intervention (multifaceted chronic disease management strategies based on the chronic care model) in improving outcomes for type 2 diabetes mellitus and hypertension using readily available resources in the Malaysian public primary care setting. This paper presents the study protocol.

**Methods/Design:**

A pragmatic cluster randomised controlled trial using participatory action research is underway in 10 public primary care clinics in Selangor and Kuala Lumpur, Malaysia. Five clinics were randomly selected to provide the EMPOWER-PAR intervention for 1 year and another five clinics continued with usual care. Each clinic consecutively recruits type 2 diabetes mellitus and hypertension patients fulfilling the inclusion and exclusion criteria over a 2-week period. The EMPOWER-PAR intervention consists of creating/strengthening a multidisciplinary chronic disease management team, training the team to use the Global Cardiovascular Risks Self-Management Booklet to support patient care and reinforcing the use of relevant clinical practice guidelines for management and prescribing. For type 2 diabetes mellitus, the primary outcome is the change in the proportion of patients achieving HbA1c < 6.5%. For hypertension without type 2 diabetes mellitus, the primary outcome is the change in the proportion of patients achieving blood pressure < 140/90 mmHg. Secondary outcomes include the proportion of patients achieving targets for serum lipid profile, body mass index and waist circumference. Other outcome measures include medication adherence levels, process of care and prescribing patterns. Patients’ assessment of their chronic disease care and providers’ perceptions, attitudes and perceived barriers in care delivery and cost-effectiveness of the intervention are also evaluated.

**Discussion:**

Results from this study will provide objective evidence of the effectiveness and cost-effectiveness of a multifaceted intervention based on the chronic care model in resource-constrained public primary care settings. The evidence should instigate crucial primary care system change in Malaysia.

**Trial Registration:**

ClinicalTrials.gov NCT01545401

## Background

Chronic diseases, led by cardiovascular diseases (CVD)—mainly ischaemic heart disease and stroke [1, 2], are the largest cause of morbidity and mortality in the world. The majority of the chronic disease burden occurs in the low- and middle-income countries [1–3]. In Malaysia, chronic conditions were responsible for 69% of the total burden of disease as measured in disability-adjusted life years (DALYs) [4]. Chronic diseases accounted for 71% of all deaths, of which 30% were caused by CVD [5]. In addition, there is a trend towards younger age at first myocardial infarction [6] and higher CVD mortality in Malaysia compared to developed countries [5]. This disturbing phenomenon is caused by the rising epidemic of cardiovascular (CV) risk factors such as hypertension (HPT) and type 2 diabetes mellitus (T2DM) over the past 30 years [1]. The National Health and Morbidity Survey 2011 showed that the prevalence of HPT and T2DM among Malaysian adults had reached epidemic proportion at 32.7% and 15.2%, respectively [7].

In Malaysia, the majority of common chronic diseases are managed in primary care [8]. This presents an enormous challenge to the primary care workforce, because resources are often limited and are further divided into the dual system of public and private primary care sectors. There is an imbalanced distribution of resources between the public and private sectors, where the number of private clinics outnumbered the public clinics by 6.3 to 1 in 2008–2009 [8]. The public sector is served by 0.52 doctors per 10,000 population, whereas the private sector is served by 2.37 doctors per 10,000 population [8]. Private primary care doctors often work in independent practices deficient of allied health support, whereas public primary care clinics are staffed by trained family physicians known as family medicine specialists (FMS), medical officers without postgraduate qualifications, paramedical practitioners known as assistant medical officers, nurses, pharmacists and dieticians/nutritionists [8]. In terms of funding, the public primary care sector is subsidised by the government and patients pay a minimal sum for treatment. In the private sector, costs are largely borne by the patients, their employers or insurance companies [9]. Therefore, it is often too expensive for patients with multiple chronic conditions to bear the out-of-pocket costs in the private sector [9]. As a result, the over-subsidised and under-staffed public primary care clinics are overburdened, providing care to a larger proportion of patients with chronic conditions (33.7/100 encounters) compared with the private primary care clinics (5.6/100 encounters) [10]. Although public primary care clinics have access to allied health care personnel, the effective implementation of multidisciplinary management of chronic diseases is often hampered by high turnover and shortages of staff, high patient load and time constraints [9]. Overall, the Malaysian primary care system is still orientated towards the care of acute, episodic illnesses [9].

The strain and limitation in the Malaysian primary care system may have contributed to the suboptimal management and control of chronic diseases. A nationwide audit of diabetes care and management conducted in public primary care clinics showed that only 18.1% of T2DM patients had attained an HbA1c of < 6.5% [11]. A study in six public primary care clinics revealed blood pressure (BP) control was achieved in 24.3% of HPT patients with T2DM and 60.1% of HPT patients without T2DM [12]. Similarly, a study looking at the process of care and the choice of antihypertensive medications in public and private primary care clinics in Malaysia revealed that 21% of prescription practices were less than optimal in both sectors [13]. A lipid control study of diabetics revealed that the target low density lipoprotein cholesterol (LDL-C) of ≤ 2.6 mmol/L was achieved in only 22% of diabetic patients attending a public primary care clinic in Sarawak, Malaysia [14].

Poor management of chronic diseases in primary care can lead to the massive burden of treating complications in secondary care, as well as burdening patients and their families because of morbidity and premature deaths, and burdening the country because of the premature loss of human capital [3]. Improving the prevention and management of chronic diseases in primary care should therefore be a priority for low- and middle-income countries [15–17]. However, when resources are limited, priorities should be given to the most cost-effective strategy that can produce swift changes [18]. An integrated and multifaceted approach to the management of chronic diseases in primary care has been shown to be cost-effective [19]. Because the majority of the chronic disease burden is caused by CVD, the World Health Organization (WHO) advocates integrated and multidisciplinary intervention in primary care, targeting those with multiple CV risk factors [20].

However, it is vital to recognise that chronic diseases management (CDM) is fundamentally different from acute care, demanding a complex health-systems response that needs to be sustained across the continuum of care [16]. CDM involves opportunistic case finding for assessing risk factors, detection of early disease and identification of high-risk patients, as well as pharmacological and psychosocial interventions. It often requires a stepped-care approach involving long-term follow-up with regular monitoring and promotion of adherence to treatment. To meet the challenge of chronic diseases, primary care systems will have to be redesigned and strengthened substantially [16, 17, 19]. Fundamental changes are needed in the way care is structured and delivered [16].

In view of the growing needs to re-orientate the health system, the WHO proposed a model for change, namely the Innovative Care for Chronic Conditions (ICCC) Framework [16]. This framework took its reference from the chronic care model (CCM), an evidence-based model developed by Wagner and colleagues [21–23]. The CCM offers a solution that shifts the paradigm from the acute care model to a comprehensive, patient-centred model of care, which integrates multifaceted elements to improve the quality of chronic disease outcomes [21–23]. It argues that optimal CDM is achieved when a well-coordinated, proactive health care team interacts productively with an empowered and motivated patient [21–23]. Evidence has shown that successful implementations of the CCM have been framed within pragmatic environments and have used collaborative and participatory approaches aiming at empowering health care providers to improve clinical practice [24]. Primary care providers should therefore be empowered with knowledge and skills and be given the autonomy to make the choice of actions within their constraints to improve their patients’ health outcomes [25].

Evidence from developed countries has shown that primary care practice redesigned in accordance with the CCM improves the quality of care and outcomes for patients with various chronic conditions [26–28]. This model has greatly influenced the reorganisation of chronic disease care in many developed countries such as Australia, the United Kingdom and the United States of America [28–31]. Experiences from previous studies have also shown that this innovative model of care results in higher short-term costs owing to the increase in resources required to change the current model of care [32]. However, recent evidence of this model’s effectiveness in reducing HbA1C and risk of end-stage renal disease could potentially translate to better quality-adjusted life years (QALY), making it cost-effective in the long run [33]. Furthermore, because the CCM relies on the innovative use of existing health care resources, the implementation of this model of care would be different from one country to another; hence, the results of cost-effectiveness analyses of such initiatives should be context- and country-specific [33].

Evidence on the effectiveness of the CCM in developing countries is also emerging [34, 35]. The CORFIS study, a pragmatic, non-randomised controlled trial involving 70 private primary care clinics in Malaysia, showed that the proportion of hypertensive patients who achieved target BP after 6 months was significantly higher in the CORFIS arm (69.6%) as compared with the control arm (57.6%), P = 0.008 [35]. The CORFIS intervention was designed based on five of the six CCM elements [35]. However, further research is needed to evaluate the effectiveness and cost-effectiveness of this intervention in the Malaysian public primary care setting, where a larger proportion of patients with chronic conditions are receiving care and where limited resources are often stretched thin. Therefore, the main aim of this study was to evaluate the effectiveness of the EMPOWER-PAR intervention (multifaceted CDM strategies designed based on the CCM) in improving clinical outcomes for patients with T2DM and/or HPT using existing health care resources in the Malaysian public primary care setting. This paper describes the design of the trial, the details of the EMPOWER-PAR intervention and its underpinning conceptual framework.

### Hypotheses

The primary hypothesis for T2DM patients was that the proportion achieving the target HbA1c of < 6.5% would improve with the EMPOWER-PAR intervention. The primary hypothesis for HPT patients without T2DM was that the proportion achieving the target BP of < 140/90 mmHg would improve with the EMPOWER-PAR intervention.

The secondary hypothesis for T2DM patients was that the proportion achieving the target BP of ≤ 130/80 mmHg would improve with the EMPOWER-PAR intervention. The secondary hypotheses for both groups of patients (T2DM and HPT without T2DM) were that the proportions achieving target fasting serum lipid, body mass index (BMI) and waist circumference (WC) would improve with the intervention. Medication adherence levels and patients’ perceptions of their experience of chronic disease care were also expected to improve with the intervention. Secondary hypotheses were also made at the primary care providers’ level in terms of the process of care and prescribing pattern, which were expected to improve with the intervention. Cost-effectiveness and primary care providers’ perceptions, attitudes, experiences and perceived barriers in implementing the intervention were also explored.

## Methods/Design

This is a pragmatic cluster randomised parallel controlled trial currently being conducted in 10 public primary care clinics in two states in Malaysia—Wilayah Persekutuan Kuala Lumpur (WPKL) and Selangor (SEL). The overall duration of the study is two years, and the duration of intervention is one year. Blinding was not possible due to the nature and complexity of the intervention. The study protocol is registered with clinicaltrial.gov (NCT01545401), and the reporting of this paper has been done in accordance with the CONSORT Statements [36–38].

The cluster randomised trial design was used because of its strengths in evaluating educational and interventional programmes in health care units [38]. The pragmatic study design was chosen to maximise external validity to ensure that the results can be generalised to the public primary care system in Malaysia [39]. The participatory action research (PAR) approach [25, 40] was adopted in the design and implementation of the EMPOWER-PAR intervention to ensure that the primary care providers involved in this study are empowered to choose between actions within their constraints to improve their patients’ health outcomes.

### Site recruitment

#### Site eligibility

All 34 clinics led by FMS in SEL and WPKL were invited to participate in the study and were given the site feasibility assessment form.

To be eligible, the clinics were required to satisfy all of the following criteria:have a minimum of 500 T2DM patients and 500 HPT patients in the registryhave an FMS who is keen to participate in the study and willing to lead the implementation of the intervention components in the clinichave the minimum capacity to implement the obligatory components of the EMPOWER-PAR interventionbe located within 70 km of the central laboratory (as the blood samples were transported back to the centre for analysis)

#### Site selection

A site feasibility assessment was conducted to identify eligible clinics. Out of the 34 sites, only 20 fulfilled the eligibility criteria to enter the study. These 20 clinics were then matched into 10 pairs according to their geographical locations, staffing and workload. Geographical location was divided into urban and suburban areas. An urban area was defined as an area located within a major city, while a suburban area was defined as the surrounding area located within commuting distance to a major city. Staffing was defined as the number of doctors and allied health personnel (FMS, medical officers, assistant medical officers, staff nurses, dieticians/nutritionists and pharmacists) working in the clinic. Workload was defined as the average number of patients seen in the clinic per day.

Multistage randomisation was performed using computer-generated tables. The first stage was to randomly select five of the 10 pairs to be included into the study. The second stage was to randomly allocate the clinics into intervention and control arms. Table 1 summarises the characteristics of the randomly selected clinics.

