**Table 1 Tab1:** **Characteristics of EMPOWER-PAR Intervention Clinics and Control Clinics**

Clinic characteristics		Geographical location	Workload (average number of patients seen in the clinic per day)	Staffing (number of doctors and allied health personnel)
Pair no. 1	**Intervention**	**Urban**	**900**	**30**
	Control	Urban	900	28
Pair no. 2	**Intervention**	**Urban**	**600**	**27**
	Control	Urban	650	29
Pair no. 3	**Intervention**	**Urban**	**550**	**32**
	Control	Urban	500	33
Pair no. 4	**Intervention**	**Sub-urban**	**500**	**22**
	Control	Sub-urban	500	20
Pair no. 5	**Intervention**	**Sub-urban**	**350**	**21**
	Control	Sub-urban	400	19

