### Statistical analysis

The statistical analysis plan to test the primary hypotheses of the study is described. Continuous variables will be described by summary statistics (means and standard deviations) for normally distributed variables. If the distribution is not normal, median with inter-quartile range will be reported instead. Other descriptive statistics, such as minimum and maximum values will be reported when necessary. Categorical (nominal/ordinal) variables will be described by frequencies with percentages. All outcomes are treated as categorical variables (e.g. proportions of patients achieving targets for HbA1c and BP). To assess the differences in the proportions of patients who are able to reach the treatment goals by their intervention strategy, a generalized estimation equation model that adjusts for clustering effects will be used. The model will be an independent working model. Treatment effects will be obtained using the estimated marginal means and differences will be tested using the Wald chi-square tests. The power of the study will be recalculated based on the effect size and after taking into account the clustering effect of the study design. An intention-to-treat analysis will be conducted, and *P-values* of less than 0.05 will be considered significant. All analyses will be carried out using SPSS (IBM Corp. Released 2011 IBM SPSS Statistics for Windows, Version 20.0. Armonk, NY: IBM Corp.).

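### Clinics were pair-matched and Table 1 keeps the pairs, but the stated primary analysis uses neither the pairs nor a matching factor and gives no reason, so its error rate depends on an unknown within-pair correlation.

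*Protocol article*

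**What the plan says.** **Design.** Under Site selection, the eligible clinics are matched: "These 20 clinics were then matched into 10 pairs according to their geographical locations, staffing and workload". Randomisation has two stages. Whole pairs were drawn first: "The first stage was to randomly select five of the 10 pairs to be included into the study". Arms were assigned after that: "The second stage was to randomly allocate the clinics into intervention and control arms". The text does not say that this step worked within pairs. Table 1 ("Characteristics of EMPOWER-PAR Intervention Clinics and Control Clinics") lists the clinics by pair number, with exactly one clinic per arm in each of five pairs, so within-pair allocation is a fair inference.

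**Analysis.** The Statistical analysis section opens: "The statistical analysis plan to test the primary hypotheses of the study is described". It then fixes the model: "a generalized estimation equation model that adjusts for clustering effects will be used". The working correlation is set to independence, and the section gives estimation and testing as follows: "Treatment effects will be obtained using the estimated marginal means and differences will be tested using the Wald chi-square tests". No pair term, stratum or matching variable is named. The two sample size sections use an unpooled two-sided Z-test for five clusters against five, also without pairing. No reason for setting the match aside appears anywhere.

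**The concern.** Clinics in a matched pair may have similar outcomes. The difference between arms then varies less than an analysis of two independent groups of five clinics assumes. How much less depends on r, the correlation between the two clinics of a pair in their outcome proportions, and the article gives no value for it.

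With only ten clinics this matters in two ways. The real type I error of the planned test shifts with r, so a nominal 5% cannot be taken at face value. Any precision that the matching bought is also not credited. Because the article does not mention the pairs in the analysis, a paired result reported later would be an unplanned alternative.

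**Working it through.** **1. What the matching achieved on the matching factors (Table 1).** Location is identical within every pair (three urban, two suburban). Workload differs by at most 50 patients a day within a pair and ranges from 350 to 900 overall. Staffing differs by at most 2 within a pair and ranges from 19 to 33. The match on these factors is close. That says nothing direct about r for HbA1c or BP control, so a range of r is used.

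**2. The plan's own power.** The sample size sections state 91% (T2DM, 63 per clinic) and 88% (HPT without T2DM, 44 per clinic) for a 25% difference, but give no ICC and no control proportion. The figures therefore cannot be reproduced from stated inputs. Assume ICC 0.05 and 25% against 50%:

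- Variance of the difference = [p1(1−p1) + p2(1−p2)] × [1 + (m−1) × ICC] / n per arm.
- T2DM: (0.1875 + 0.25) × 4.10 / 315 = 0.005694; SE 0.0755; 0.25/SE = 3.313; Z-test power 91%.
- HPT: 0.4375 × 3.15 / 220 = 0.006264; SE 0.0791; 0.25/SE = 3.159; Z-test power 88%.

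These assumptions match both stated powers (n is 5 × 63 and 5 × 44). The Background rates would also serve: 18.1% to 43.1% needs ICC 0.057, and 60.1% to 85.1% needs ICC 0.065. Those inputs move the t-test powers below by about one point or less.

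**3. Type I error at nominal 5%.** Five pairs of normal clinic means were simulated with within-pair correlation r. The stand-in for the planned test is the difference in arm means over an uncorrected sandwich SE, compared with 1.96.

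| r | Wald, pairs ignored | Unpaired t, 8 df | Paired t, 4 df |
|---|---|---|---|
| 0 | 11.8% | 5.0% | 5.0% |
| 0.2 | 8.7% | 3.3% | 5.0% |
| 0.4 | 5.7% | 2.0% | 5.0% |
| 0.6 | 3.0% | 0.9% | 5.0% |

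The Wald test passes through 5% at about r = 0.45. Adding a pair term and keeping an uncorrected Wald test gives about 15% at every r.

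**4. Power, T2DM/HPT.** Paired power is noncentral t on 4 df with noncentrality 3.313/√(1−r) or 3.159/√(1−r). The unpaired power is simulated, because the same r also reduces the true variance of the unpaired difference.

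| r | Paired t, 4 df | Unpaired t, 8 df |
|---|---|---|
| 0 | 70%/66% | 83%/79% |
| 0.3 | 84%/80% | 86%/82% |
| 0.5 | 93%/91% | 88%/84% |

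The two tests are equal at about r = 0.35 (86%/83% for paired, 86%/82% for unpaired).

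**5. Adjusting for location only.** A clinic-level model with arm and urban/suburban leaves 10 − 3 = 7 df, and the critical value rises from 2.306 to 2.365. If location is unrelated to outcome, power goes from 83%/79% to 81%/77%. If location is assumed to explain 20% of the variance of the clinic proportions, simulated power is 88%/86% against 83%/79% without the factor, and type I error stays at 5%.

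**The case against.** **Ignoring the pairs is legitimate.** It adds no bias, and an unpaired cluster-level t-test never exceeds its nominal level. With five pairs, a deliberate unmatched analysis can be defended because it keeps 8 df instead of 4. This stands. A reader might infer from the mismatch with the randomisation that the planned analysis is invalid or its estimate biased; the documents do not support that. What remains is that the article makes no such argument, and the test it names is a Wald chi-square with no stated small-sample correction, not a t-test on 8 df.

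**The direction is not fixed.** A reader might also infer that ignoring the match simply makes the standard error too large. For the named test that is true only above about r = 0.45. Below that it is liberal, which is a small-sample fault and not a matching fault. This stands too, and it is why the remedy must deal with both.

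**Nothing shows that matching worked on outcomes.** Pairs were not matched on baseline control, and the article attributes differences between clinics partly to the lead specialist's experience and length of service, which were not matched. At low r a paired primary would cost 13 points of power. This rules out recommending pairing as the primary analysis.

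**An unseen analysis plan may name the terms.** That is possible. But the section says that it describes the plan for the primary hypotheses, and it goes down to the working correlation and the test. It also commits to one model, so the documents do not support a reading that the paired or unpaired choice was deliberately left open.

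**Conclusion.** The point holds as a recommended improvement, not as a fault that invalidates the trial. The design is pair-matched, the described primary analysis uses neither pairs nor matching factors, and no reason is given. The treatment estimate is unaffected. The type I error of the named test runs from about 12% at r = 0 to 3% at r = 0.6, and r is unknown.

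It may be tempting to conclude that a paired primary analysis is plainly better. It is better only above about r = 0.35 and clearly worse near zero, and nothing in the article says where r lies.

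The error rates rest on normal clinic means, equal clinic sizes and a Wald test without small-sample correction. The power figures rest on an assumed ICC and assumed proportions chosen to match the stated powers. Within-pair allocation is read from Table 1.

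**What to change.** Add to the Statistical analysis section, before the arms are compared (Trial status says that cleaning and analysis had only just started):

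- Primary analysis: adjust for the matching factor urban/suburban and use a small-sample reference distribution, for example a clinic-level model of the outcome proportion on arm and location with t on 7 df.
- Fixed sensitivity analysis: the mean of the five within-pair differences with a t interval on 4 df, which keeps 5% error at every r. An exact within-pair permutation test is no substitute, since its smallest two-sided p-value is 2/32 = 0.0625.
- One sentence saying why the pairs are not in the primary model.

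A pair term in an uncorrected Wald GEE should not be used. Location adjustment does not remove all dependence on r: correlation from other sources leaves the 7-df test conservative (about 2% at r = 0.4 in the same simulation), which is why the paired result is needed beside it.

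Cost: a few sentences, minor coding and no new data. The downside is one degree of freedom, at most about 2 points of power if location is unrelated to outcome.

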### Patient recruitment

This study recruited consecutive T2DM and/or HPT patients who attend the selected clinic within the 2-week recruitment period. These patients were given the patient information sheet in the waiting area. Informed consent forms were obtained from those willing to participate. Screening was conducted to identify eligible participants based on the inclusion and exclusion criteria. Eligible patients were then enrolled in the study.

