#### Phase 3: Facilitation and support to implement the intervention

Each clinic was assigned two facilitators to coach the CDM team, facilitate and guide the implementation of intervention and provide feedback on their performance. Facilitators were the investigators, all of whom are qualified FMS or clinical epidemiologists. The facilitators conducted two follow-up site visits over the 1-year intervention period. The visits occur at 3 months and 9 months. During the visits, the facilitators met the CDM team to collect information on the implementation process, discuss the challenges and document the progress in the clinics. Similar data were also collected during the intervention review workshop at 6 months. This information was analysed, and detailed feedback were then provided to each clinic. It is believed that, through this collaborative process of coaching and feedback sessions, optimal implementations tailored to the needs of each clinic could be achieved.

The control clinics continued with usual care with no additional intervention. The CDM workshop modules and intervention tools will be made available to the control clinics at the end of the study. There were no other additional resources allocated to either the intervention or the control group.

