### Ethical considerations

The Ethics committee of UiTM and the Medical Research Ethics Committee (MREC) of the Ministry of Health (MOH) approved the study protocol. Permission from the Family Health Development Division (FHDD) of the MOH and the respective Health District Offices was also obtained prior to the conduct of the study. The study was conducted in accordance with the Declaration of Helsinki and Good Clinical Practice (GCP) requirements [68]. Patient information sheets were distributed, and informed consent was obtained from all participants prior to their study enrolment. For participants who were unable to read, the content of the consent form was read aloud to them, and a copy of the patient information sheet was given to their next of kin with additional explanation given if needed. Confidentiality of personal information was ensured at all times. Subject enrolment was done by the investigators and not the subjects’ attending doctors to reduce subjects’ perceived coercion to participate in the study. Subjects were informed of any immediate results obtained from the study that might affect their care or health.

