### Trial status

Site feasibility assessment and recruitment were conducted in January–May 2012. Patient recruitment and baseline data collection were conducted in June–December 2012. The EMPOWER-PAR intervention was delivered in January–December 2013. Outcome data were collected in January–June 2014. At the time of submission of the manuscript, data cleaning and analysis has just started.

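### As described, clinics were allocated to arms during site recruitment, apparently before unblinded investigators enrolled patients, so entry to each arm was open to knowledge of the allocation

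*Protocol article*

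**What the plan says.** The protocol article describes a two-stage randomisation under Site selection, a subsection of Site recruitment. Five of ten matched pairs were drawn first. Then: "The second stage was to randomly allocate the clinics into intervention and control arms". Table 1 lists the selected clinics by arm.

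Patient recruitment comes next: "This study recruited consecutive T2DM and/or HPT patients who attend the selected clinic within the 2-week recruitment period". Those willing gave consent and were then screened. Under Ethical considerations, "Subject enrolment was done by the investigators" rather than by the attending doctors, and the reason given is to reduce perceived coercion. The opening of Methods/Design says that blinding was not possible.

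Trial status supplies the dates: "Site feasibility assessment and recruitment were conducted in January–May 2012. Patient recruitment and baseline data collection were conducted in June–December 2012", and then "The EMPOWER-PAR intervention was delivered in January–December 2013". Under Phase 3, "Facilitators were the investigators, all of whom are qualified FMS or clinical epidemiologists".

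The article gives no calendar date for the allocation. It does not say that the arm was hidden from recruiters, clinics or patients while baseline was under way.

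**The concern.** Randomising clinics protects the comparison only if each clinic's patient sample is formed without knowledge of the arm. If the recruiter, the clinic or the patient knows the arm, that knowledge can affect who is approached, who agrees and how a borderline exclusion is judged. The arms can then differ in the kind of patient they hold, and the estimated effect mixes intervention with selection.

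The trait that matters most is willingness to engage. The Exclusion criteria section requires intervention-arm patients to see the chronic disease management (CDM) team at least twice and counts the others as lost. A recruiter who knows the arm could lean towards likely attenders, or patients could select themselves. Adjusting for baseline HbA1c or blood pressure does not capture such a trait. With five clinics per arm, selection and chance imbalance are hard to tell apart afterwards.

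**Working it through.** **1. Order of events.**
- Site feasibility assessment and recruitment, the heading under which allocation is described: January–May 2012.
- Patient recruitment and baseline: June–December 2012.
- Delivery: January–December 2013.

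If allocation fell inside the first window, the gap to a given clinic's recruitment runs from days or weeks (late May to early June) to about 11 months (January to December). Matching required all 20 eligible clinics to be identified first, so a date late in the window is plausible. The order is therefore apparent, but the length of the gap is not known.

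**2. Who could act on the arm.** Enrolment was by investigators in an unblinded trial. The stated reason for not blinding is the nature of the intervention, but nothing was being delivered during baseline, so that reason does not rule out concealing the arm at that point.

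**3. What selection would do to the stated outcome.** Primary outcomes defines a change in the proportion at target. The two sample size sections likewise speak of a difference from baseline and between groups. Assume no true effect.

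*Selection on baseline control.* Let the intervention arm start with an excess d at target, of which a fraction r persists at one year. The spurious difference in change is r·d − d = −(1 − r)·d. At r = 1 it is zero. With an assumed d = 5 points and r = 0.5 it is −(1 − 0.5) × 5 = −2.5 points, against the intervention.

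*Selection on motivation.* Let m_I and m_C be the shares of motivated recruits in the intervention and control arms. Let g1 and g0 be the changes in attainment among motivated and other patients under usual care. The spurious difference in change is (m_I − m_C)·(g1 − g0). It favours the intervention if its clinics recruit more motivated patients and such patients improve more, and it can go the other way. The article gives none of these quantities, so neither size nor sign can be derived.

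**4. Does delayed allocation change the sample size?** First the plan's own figures: 313/0.75 = 417.3, rounded up to 418 per arm, or 836 type 2 diabetes patients; 219/0.75 = 292 per arm, or 584 hypertension patients. Both reproduce. No input (cluster number, cluster size, difference, power, dropout) depends on when the arm is revealed, so 836 and 584 stand.

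**5. Does delayed allocation fit the calendar?** Baseline closes by December 2012 and delivery opens in January 2013. Allocation pair by pair fits. A pair finishing in December has about a month or less of notice; earlier pairs have more.

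**The case against.** Real safeguards are described. Patients were consecutive attenders in a fixed two-week window, information was handed out in the waiting area, and the attending doctors did not enrol. Most exclusions are matters of fact, such as type 1 diabetes, dialysis, pregnancy or a blood pressure threshold. A condensed article may also leave the timing and concealment of allocation to the full protocol, and the trial profile figure is not available here. All of this stands and lowers the risk. It does not close it: consent remains a choice, consecutive approach depends on the person approaching, and exclusions for shared care or for disorders needing referral involve some judgement.

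Several stronger readings are tempting, and the article does not support them.
- *Arms were known months before any patient was seen.* No allocation date is given; the gap could be weeks.
- *Better-controlled recruits in intervention clinics would inflate the benefit.* Step 3 shows that for a change from baseline such selection gives zero or a negative difference. A gap at a single time point, and any false-positive rate built on it, does not carry over to the stated outcome. The Statistical analysis section is less specific about change, but the outcome and sample size sections are clear.
- *The same individuals recruited and coached.* Facilitators and enrollers were both investigators; that they were the same people in the same clinics is not stated.
- *Delayed allocation is free.* Intervention clinics had to form a team of at least five, attend three workshops of 1.5 days (4.5 days in all) and prepare a plan. Workshop dates are not given.
- *Heavy clinic workloads prove room for selection.* The cited encounter rate covers all chronic conditions, not distinct eligible patients, and consecutive recruitment up to a target would give the same low ratio.

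**Conclusion.** The point holds as a weakness in the order of allocation and recruitment. On the article's account, arms were assigned within site recruitment, unblinded investigators then enrolled patients, and no concealment during that period is described. Entry was therefore exposed to knowledge of the arm, with partial safeguards. This rests on reading the section placement together with the Trial status dates; a statement that the arm was concealed until baseline closed would remove it.

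The article does not show that selection occurred. Its possible effect on the change in target attainment cannot be sized or signed. The change of order would have left both sample sizes untouched and fitted the stated calendar, so it was worth making.

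**What to change.** **Design.** Keep the random choice of five pairs before recruitment. Have someone not involved in recruitment generate the within-pair allocation, and reveal it only when both clinics of the pair have completed baseline and before delivery starts in January 2013. This needs no extra patients or visits. The cost is shorter lead time for team formation and workshops, about a month or less for clinics finishing in December. It addresses recruitment bias only; unblinded follow-up and the two-visit rule in the intervention arm are unaffected.

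**This trial.** Recruitment, delivery and outcome collection are complete and analysis has just begun, so the order can no longer be changed. The report should:
- state when the allocation was made and who knew it during recruitment;
- tabulate numbers attended, approached, eligible and consented, and baseline target attainment, by clinic within pair;
- limit the conclusion by naming recruitment bias as a possible explanation of the result. Balanced tables would not exclude selection on unmeasured traits, and with five clinics per arm some imbalance is expected by chance.

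The cost is a paragraph and a table, provided that screening counts were kept; if they were not, the report should say so.
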